## Abstract

**Background:**

Psychiatric patients are more likely to be victims of crime than others in the community. Dual diagnosis patients with comorbid psychiatric and substance use disorders are especially prone to victimization. Victimization is associated with substance abuse, more severe symptomatology and homelessness. There is a strong need for interventions to reduce victimization in this population. We developed the Self-wise, Other-wise, Streetwise (SOS) training to reduce victimization in patients with dual diagnosis.

**Methods/design:**

This study is a randomized controlled trial using a parallel group design to determine the effectiveness of adding the SOS training to care as usual. Patients with dual diagnosis (*N* = 250) will be allocated to either care as usual plus SOS training (*N* = 125) or care as usual only (*N* = 125) using computer-generated stratified block randomization. To compare effectiveness participants will be interviewed at baseline and 2, 8 and 14 months follow-up. The primary outcome measure is treatment response (yes/no), defined as either no victimization at 14 months follow-up or at least a 50 % reduction in incidents of victimization at 14 months follow-up compared to baseline assessment. Victimization is measured with the Safety Monitor, an adequate self-report instrument used by Statistics Netherlands to measure victimization on a large scale in the Netherlands. Outcome assessors are blind to treatment allocation. An economic evaluation will be performed alongside the randomized controlled trial and will take the societal perspective.

**Discussion:**

This study is the first randomized controlled trial to examine the effectiveness of an intervention that aims to reduce victimization in patients with dual diagnosis. If the intervention is effective it can be implemented in mental health care and contribute to the safety and well-being of patients.

**Trial registration:**

Dutch Trial Register (NTR): 4472, date of registration: 24-03-2014.

## Background

In contrast to what the general public assumes, psychiatric patients are more often victims of crime than perpetrators [1–3]. A systematic review on the prevalence of violent victimization of patients with severe mental illness (SMI) indicates that these patients are more likely to be violently victimized than other community members [2]. In addition to violent victimization, psychiatric patients are more often a victim of property crime [3]. Recent research in the Netherlands showed an annual prevalence rate of victimization in SMI outpatients of 47 % compared to 32 % in the general population [4]. Dual diagnosis patients with comorbid psychiatric and substance use disorders are especially prone to victimization [2, 5, 6]. These patients are approximately 1.3–5.4 times more likely to be violently victimized than psychiatric patients without substance use disorders [2, 5].

Victimization is associated with physical injury, psychological distress and impaired occupational functioning [7–9], but also with posttraumatic stress disorder, major depression, substance abuse and difficulties with emotion regulation and assertiveness [7, 9–13]. In SMI patients, victimization is associated with more severe symptomatology and poorer illness course [14–16], more substance abuse [14, 15, 17, 18], depression [18], homelessness [15, 17], violent behavior [19], offending [20] and interpersonal problems [21]. In substance-dependent patients, victimization is associated with psychological distress [22], worse psychiatric status, more psychiatric hospitalizations and outpatient treatment, worse general level of functioning [23], worse addiction illness-course [24] and offending [25].

Since most studies used cross-sectional designs, the exact mechanisms behind these associations remain unclear. It is however plausible that these problems associated with victimization, such as substance abuse, more severe symptomatology and homelessness, are consequences as well as predictors of victimization [12, 14, 24, 26–28]; This may cause a destructive vicious cycle of victimization, substance use and severe symptomatology. In line with this is the finding that an accurate predictor of victimization is having a history of victimization [26, 29–32]. One explanation of this victimization-revictimization link is that some are more prone to become a victim than others, due to personal characteristics, lifestyle and living environment [33, 34]. There is however evidence that revictimization is partly the result of changes following victimization, like emotion dysregulation, more substance use, offending, depression and posttraumatic stress disorder [12, 24, 32, 35].

Victimization of patients is an important concern not only because of its huge effect on mental and physical health, but also because of the significant societal and economic consequences of violence, due to increased burden on social services, healthcare and justice systems and productivity losses [36]. Reducing victimization in psychiatric patients may have long-lasting effects on personal well-being, the number of criminal offenses in society and economic costs. Consequently, there is a strong need for interventions to reduce victimization in psychiatric patients [2–4, 37–39]. Patients with dual diagnosis are the most vulnerable to victimization [2, 3, 5]. There is a lack of evidence-based treatment options for patients with substance use disorders co-occurring with severe mental illness [40] or posttraumatic stress disorder [41]. Therefore, we developed an intervention, the Self-wise, Other-wise, Streetwise (SOS) training, that aims to reduce vulnerability to victimization in patients with dual diagnosis.

SOS training focusses on the modifiable risk factors for victimization, which are subdivided into three different themes, represented in three training modules. The module *Self-wise* targets emotion regulation skills, the module *Other-wise* targets assertiveness and conflict resolution skills and the module *Streetwise* targets knowledge and skills to enhance personal safety and reduce vulnerability. As no evidence-based interventions are available so far, SOS training is based on evidence based treatment programs in other patient groups that target these skills [42–46]. SOS training is adapted to the needs of patients with substance use disorders co-occurring with any other mental disorders and can therefore be widely used in clinical practice.

By adding SOS training to care as usual (CAU) we expect patients to improve on psychopathology, emotion regulation skills, interpersonal problems and self-esteem. Besides, adding SOS training to CAU is expected to result in a decrease in substance use. We expect that these improvements will result in a reduction of victimization.

### Aims of the trial

This study aims to investigate the effectiveness of SOS training in reducing victimization of patients with dual diagnosis.

The primary research question is:Does adding SOS training to CAU result in a larger reduction of victimization compared to CAU alone?

Secondary research questions are:2.Does adding SOS training to CAU result in a larger improvement on secondary outcome measures compared to CAU alone?3.How do costs and effects of SOS training + CAU compare to CAU from a societal perspective?

## Methods/design

### Design

This study is a single-blind two-arm randomized controlled trial using a parallel group design to determine the effectiveness of adding SOS training to CAU. Participants will be interviewed at baseline and 2, 8 and 14 months follow-up. After baseline assessment, participants will be randomly allocated to either CAU + SOS training or CAU.

### Participants

Participants will be recruited in an addiction-psychiatry clinic and an addiction-psychiatry outpatient care facility in Amsterdam. Inclusion criteria are (1) 18 years of age or older; (2) substance dependence or substance abuse (involving alcohol and/or illegal drugs, including cannabis) according to Diagnostic and Statistical Manual of Mental Disorders-IV (DSM-IV) criteria; and (3) at least one other mental disorder on DSM-IV Axis I or II. Patients are excluded from the study if they (1) do not have sufficient understanding of the Dutch language; or (2) are not eligible for group therapy according to their case manager, due to for instance severe anti-social or psychopathic traits; (3) are not willing to provide informed consent. Based on a priori power analysis, we aim to include 250 (2x125) participants in this study.

### Interventions

#### Self-wise, Other-wise, Streetwise (SOS) training

The experimental add-on intervention, SOS training, is a 12 session group-based training [47]. Sessions take place twice a week and take 75 min. Each session utilizes learning techniques such as role playing, visual material, group discussions and sharing experiences. The trainers create a safe and respectful environment. Participants can give each other tokens of appreciation during every session, in order to reinforce desirable behaviour. These tokens are cards with coloured stars. By using the tokens, participants learn to reinforce and support each other. Furthermore, the tokens stimulate the participants to listen to and interact with each other. The training comprises 3 modules, *Self-wise, Other-wise* and *Streetwise.* Each module consists of 4 sessions. There is no specific order in which participants follow these modules.

The module *Self-wise* involves a transdiagnostic emotion regulation skills training. Emotion regulation refers to the ability to monitor, evaluate and modify emotional reactions to accomplish one’s goals [48]. Emotion dysregulation is a predictor of victimization [12, 49–51]. Lack of emotional awareness, for instance the inability to recognize and interpret fear cues, impairs risk perception [12, 52]. Poor risk perception increases the risk for victimization [49, 52]. Emotion dysregulation, especially impulsivity, also increases the likelihood of entering a risky situation and makes it more difficult to leave or adequately cope with a dangerous situation [12, 52]. Even small increases in emotion regulation can impact victimization risk substantially [12]. Since no evidence-based emotion regulation skills training is available for our target group, the content of *Self-wise* is inspired by elements of affect regulation therapy for major depressive disorder [42], anger management training for people with intellectual disabilities [43], skills training in affect and interpersonal regulation for patients with posttraumatic stress disorder related to childhood abuse [44] and the system training for emotional predictability and problem solving for patients with borderline personality disorder [45]. *Self-wise* is a new, simplified emotion regulation skills training suitable for patients with dual diagnosis, based on the principles of these interventions.

The module *Other-wise* involves a conflict resolution skills training. Offending, violent behaviour, interpersonal problems and lack of assertiveness increase the risk for victimization [13, 19–21, 25]. Aggressive responses to provocation can easily lead to an escalation of violence. On the other hand, non-assertive responses can provoke manipulation and exploitation. The content of *Other-wise* is inspired by social skills training for patients with schizophrenia [46]. In this module patients compose a list of important skills for preventing and resolving conflicts, which are practiced in role-playing exercises categorized by theme. Examples of these themes are: Responding to Frustrating Situations, Handling Bad News and Leaving Unsafe Situations. The specific role-playing exercises within these themes are based on input from dual diagnosis patients and mental health professionals working with these patients.

The module *Streetwise* involves a street skills training. It has been suggested that teaching patients about changeable factors that contribute to their risk of victimization may be effective in reducing victimization [37, 53–55]. *Streetwise* builds on the suggested strategies that make patients reflect on the safety of their environment and their own contribution to safety. An important aspect of *Streetwise* is safety regarding drug related behaviour and contact with drug dealers. All knowledge and skills are transferred in a playful, stimulating manner, using role-play and creative exercises.

#### CAU: Care as usual

Most participants will suffer from chronic mental health problems. Hence, CAU is an ongoing treatment process. CAU usually consists of pharmacotherapy in combination with a form of case management, for instance assertive community treatment [56]. In addition, since SOS training will be imbedded in addiction-psychiatry treatment programs, when enrolling in this study most participants will attend some form of psychosocial therapy. Depending on the participants’ motivation, capacities and needs this may include: cognitive behavioural therapy [57], motivational interviewing [58], substance abuse management training [59], social skills training, psychomotor therapy and mindfulness. The type and amount of care received by participants will be recorded.

#### Therapists

SOS training will be implemented in the treatment programs of an addiction-psychiatry dual diagnosis clinic and an addiction-psychiatry outpatient care facility of Arkin Mental Health Care, division Mentrum. Arkin is an Amsterdam-based public mental health care treatment facility. Eight employees are selected to be trained to deliver the intervention. These SOS-trainers work in various positions, for instance as psychologist, nurse or social worker. All have ample experience in working with psychiatric patients with substance use disorders and are motivated to implement this new intervention. The SOS-trainers will follow a detailed training manual which describes each training session. Each session will be led by an SOS-trainer accompanied by an SOS-co-trainer.

#### Therapist education

The education for SOS-trainers includes: studying the SOS training manual independently and two 3-h group training sessions, which will be provided by one of the researchers. The first group training session consists of: the theoretical framework of SOS training, an explanation of the exercises in module Streetwise and practising these exercises. The second group training session consists of: an explanation of the exercises in module Self-wise and Other-wise and practising these exercises. The researcher who provides the education for SOS-trainers will be present at the delivery of the first 12 sessions SOS training on both locations, to provide additional feedback to the SOS-trainers after each session. Thereafter, this researcher will attend an SOS training session at least once every month on both locations. After 6 months, an individual evaluation will be held with every SOS-trainer.

### Procedure

#### Recruitment and consent

Patients will be recruited in an addiction-psychiatry dual diagnosis clinic and an addiction-psychiatry outpatient care facility. All patients who fit the inclusion criteria, will be informed and invited by their mental health care facility. Participants will receive a participation compensation of 15 Euros per assessment for T0, T1 and T2 and 30 Euros for T3. Written informed consent will be provided before the first assessment takes place.

### Randomization and treatment allocation

Participants will be allocated to CAU + SOS training or CAU by an independent researcher using a computer-generated block randomization schedule. Randomization will be stratified by two prognostic factors: treatment centre (clinic/outpatient care) and victimization in the year prior to baseline (yes/no). Block size varies randomly. To prevent selection bias, the research coordinator and outcome assessors are denied access to the randomization schedule and are blind to block size and order.

#### Trial flow

Figure 1 provides an overview of the trial flow diagram. After informed consent is provided and baseline assessment (T0) has taken place, participants will be randomized and allocated to either CAU + SOS training or continue to receive CAU. Follow-up assessments will take place 2, 8 and 14 months after baseline assessment. For participants allocated to trial arm CAU + SOS training this will correspond to immediately, 6 months and 12 months after the completion of SOS training.

**Fig. 1 Fig1:**
[figure not shown]
Flow chart of the study design

### Measurements

Table 1 provides an overview of the measurement instruments. All instruments will be administered in the form of an interview, by a junior researcher (MSc in Psychology) or master student (holding a BSc) in clinical psychology. To minimize bias, the junior researcher will train the master student in carefully collecting data and interviewing participants. This training will start with two days consisting of explanation and role plays. After that, the master student will watch the junior researcher administer assessments. Finally, the junior researcher will supervise the first assessments administered by the master student and give feedback.

**Table 1 Tab1:** Overview of measurement instruments

Measurement instrument	T0	T1	T2	T3^a^
Safety Monitor	x			x
Questions regarding likelihood and controllability of victimization	x	x	x	x
Timeline Followback	x	x	x	x
Alcohol Use Disorder Identification Test	x		x	x
Drug Use Disorder Identification Test	x		x	x
Brief Psychiatric Rating Scale	x	x	x	x
Kessler psychological distress scale	x	x	x	x
Difficulties in Emotion Regulation Scale	x	x	x	x
Dimensions of Anger Reactions	x	x	x	x
Inventory of Interpersonal Problems	x	x	x	x
Self Esteem Rating Scale	x	x	x	x
EuroQol 5D	x	x	x	x
Manchester Short Assessment of Quality of Life	x	x	x	x
Trimbos questionnaire on Costs associated with Psychiatric illness		x	x	x
Jellinek PTSD Screening Questionnaire	x			x
Posttraumatic Diagnostic Scale	x			x
Mini-Mental State Examination	x			
Client Satisfaction Questionnaire		x	x	x

^a^
*T0* baseline, *T1* 2 months follow-up, *T2* 8 months follow-up, *T3* 14 months follow-up

Both outcome assessors will be blind to the trial arm to which the participant is allocated after randomization. To verify blinding, after each follow-up assessment the assessor will record to which trial arm he/she thinks the participant is allocated. Furthermore, the assessor will record his/her confidence regarding these thoughts on allocation.

### Primary outcome measure: victimization

Victimization will be measured with the Dutch version of the Safety Monitor (in Dutch: Veiligheidsmonitor, VM section 4), developed by the Dutch Ministry of Security and Justice [60]. The Safety Monitor is an instrument used by Statistics Netherlands (CBS) to measure victimization on a large scale (almost 80 thousand cases a year). It is an adequate self-report instrument that strongly resembles the International Crime Victimization Survey (ICVS) [61]. Section 4 of the Safety Monitor assesses victimization of 11 different crimes, subdivided in three categories:violent crimes, consisting of: sexual crimes, threats and assaults;property crimes, consisting of: burglary, theft from car, car theft, motor vehicle theft, bicycle theft, robbery and theft of other property;vandalism;

The Safety Monitor examines whether participants experienced each specific crime in the last 5 years. If so, they are asked whether they experienced that crime in the last 12 months. For each crime reported, participants are asked how frequently they experienced that crime in the last 12 months.

The primary outcome measure is treatment response (yes/no), defined as either no victimization at T3 or at least a 50 % reduction in incidents of victimization at T3 compared to T0. Since there are no previous randomized controlled trials available that aimed to reduce victimization in this target group, our treatment response criteria are based on experts opinions. Mental health care professionals working with dual diagnosis patients indicated a 50 % reduction in incidents of victimization as a clinically relevant and achievable goal.

### Key secondary outcome measures

#### Violent victimization and property victimization

The Safety Monitor subcategories violent victimization and property victimization will be examined separately.

#### Substance use (disorders)

Substance use in the past 90 days will be measured with the Timeline Followback (TLFB) [62], which has good reported reliability and validity in dual diagnosis populations [63, 64]. Using calendars, beginning on the day of assessment and working backwards, participants reconstruct daily substance use.

The Alcohol Use Disorder Identification Test (AUDIT) [65], developed by the World Health Organization (WHO) will be included to measure alcohol consumption burden. The AUDIT has shown good reliability and validity in various target groups [66] including individuals with severe mental illness [66–68]. The Drug Use Disorder Identification Test (DUDIT) [69], developed as a parallel instrument to the AUDIT, will be included to measure drug consumption burden. The DUDIT has shown good reliability and validity in individuals with psychosis [70] and in substance abusers in various treatment settings [69, 71].

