#### Within-day relationship victimization and substance use

The within-day relationship between victimization and substance use will be examined with the TLFB [62]. First, substance use will be administered with the TLFB, using calendars, as described in the section ‘secondary outcome measures’. Thereafter participants will reconstruct victimization in the past 90 days, following the same procedure, beginning on the day of assessment and working backwards. For each day on which both victimization and substance use are reported, the within-day process will be examined. Participants will be asked to indicate whether they used substances before being victimized, after being victimized, or both. The TLFB has previously been used to assess partner violence and victimization and their within-day relation to substance use [90–93].

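### The 90-day Timeline Followback at the 2-month visit reaches about 29 days back before baseline, so about a third of the T1 substance use measure precedes randomization and is also counted at T0

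*Protocol article*

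**What the plan says.** Four statements in the protocol article fix the measurement.

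- **Window.** Under Substance use (disorders), a key secondary outcome: "Substance use in the past 90 days will be measured with the Timeline Followback (TLFB"). The calendar is anchored at the visit: "beginning on the day of assessment and working backwards, participants reconstruct daily substance use".
- **Visits.** Table 1 under Measurements marks the instrument at all four assessments: "Timeline Followback x x x x".
- **Timing.** Under Trial flow: "Follow-up assessments will take place 2, 8 and 14 months after baseline assessment".
- **Randomization.** Under Design: "After baseline assessment, participants will be randomly allocated to either CAU + SOS training or CAU".

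The Effectiveness section assigns secondary outcomes to a generalized linear mixed model. It does not define the variable derived from the Timeline Followback (TLFB) or name a T1 contrast. Nothing in the article shortens the T1 window, restricts it to days after randomization, or leaves T1 out of the substance use analysis.

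**The concern.** A 90-day look-back at a visit about 61 days after baseline must include days before baseline. Those days cannot respond to the allocated treatment, and they have already been counted at T0. A T1 total taken over the whole window mixes treated and untreated time, while the T2 and T3 totals do not. A steady effect would then look as if it grew after T1.

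The Background names a decrease in substance use as an expected effect of the training and as part of the route to less victimization. T1 is the visit at the end of training. Table 1 gives neither the AUDIT nor the DUDIT at T1, so the TLFB is the only substance use instrument there. The primary outcome avoids this problem: the Safety Monitor looks back 12 months and is given at T0 and T3, 14 months apart.

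**Working it through.** **Plan's own figure.** The article gives no calculation for the TLFB. Its only design calculation, for the primary outcome (50% versus 30%, two-sided α .05, power .80), reproduces at 93 per arm and 186 in total. With 25% drop-out, 186/0.75 = 248, against 250 stated. The present point does not depend on it.

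**Inputs.** Look-back 90 days; T1 at 2 months, taken as 60.9 days (two average calendar months); T2 at 8 and T3 at 14 months; randomization after T0, with the gap not stated.

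**Step 1: overlap at T1.** Days before T0 in the window = 90 − (days from T0 to T1).

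| T1 at day | Days before T0 | Share of 90 |
|---|---|---|
| 56 | 34 | 38% |
| 60 | 30 | 33% |
| 60.9 | 29.1 | 32% |
| 62 | 28 | 31% |

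All these days also lie in the T0 window, which covers the 90 days before T0.

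**Step 2: gap before randomization.** Any gap adds to the share. For assumed gaps of 3, 7 and 14 days: 32.1/90 = 36%, 36.1/90 = 40%, 43.1/90 = 48%.

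**Step 3: T2 and T3.** The windows start at 8 × 30.44 − 90 ≈ day 154 and 14 × 30.44 − 90 ≈ day 336 after T0. Neither overlaps baseline.

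**Step 4: dilution.** If treatment changes daily use by d from day 0, the 90-day T1 average changes by d × 61/90 ≈ 0.68d. At T2 and T3 it changes by the full d. This needs no distributional assumption.

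**Step 5: illustrative power.** The reference is an analysis of the 61 post-baseline days with an assumed power of 80%. If the overlapping window has r times the standardized effect of that analysis, power = Φ((1.960 + 0.842) × r − 1.960).

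To obtain r, daily use was modelled as a person effect plus an AR(1) residual. The assumptions were a person share of daily variance of 0.3 to 0.7, autocorrelation of 0 to 0.98, and a constant effect from day 0.

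- With the T0 measure as covariate, r is about 0.85 to 0.92, and power is about 0.66 to 0.73.
- Without T0 adjustment, r is about 0.68 to 0.72, and power is about 0.48 to 0.53. The lower end is r = 61/90: Φ(2.802 × 0.678 − 1.960) = Φ(−0.06) ≈ 0.48.

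Baseline adjustment softens the loss because the T0 measure partly explains the shared days.

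**The case against.** The best defence is that the article fixes what is collected, not what is analysed. It describes a daily calendar, defines no derived variable, and leaves the model general. An unseen analysis plan could drop the pre-baseline days, and asking for 90 days at T1 loses nothing because the 61 useful days are a subset. This stands in part: the harm follows only if the 90-day total is used, and the remedy lies in the analysis. But the outcome is described as use over the past 90 days, at a visit where that period overlaps baseline. That is a stated rule that misleads if followed, not a detail left open.

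Some stronger readings are tempting but not supported.

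- *Power at T1 falls from 80% to 48%.* This holds only without baseline adjustment, and the article states no power for the TLFB.
- *The planned model treats T1 as wholly post-randomization.* The article specifies neither time coding nor visit contrasts.
- *More than half of the window is unaffected.* If about six weeks of training (12 sessions, two a week) end exactly at T1, 90 − 42 = 48 days (53%) precede the first session. That depends on when each participant starts. Time between randomization and the first session is also properly part of an intention-to-treat comparison.
- *A victimization outcome is diluted in the same way.* The calendar does overlap there too ("Thereafter participants will reconstruct victimization in the past 90 days"), but that section concerns a within-day relationship listed among other variables of interest, not a treatment outcome.

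**Conclusion.** The point holds in a limited form. As written, about 29 of the 90 days in the T1 substance use measure (32%; 31 to 38% for T1 between day 62 and day 56) precede baseline and are counted twice. Any gap before randomization raises the share. If the 90-day total is used in the treatment comparison, a constant effect on daily use shows at about 0.68 of its size at T1 and falsely looks smaller than at T2 and T3.

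Because the overlap is the same in both arms, it pulls the contrast towards no effect and cannot by itself create a benefit. It affects one visit of one key secondary instrument. The overlap and the 0.68 rest on the article's schedule, the second also on an effect that is constant from day 0. The power figures are illustrations under assumed correlations and should not be cited as properties of the trial.

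**What to change.** State that at T1 only days after randomization, or at least after the T0 assessment, enter the substance use outcome. Analyse use days out of days observed, with a binomial model or a count model with a log-days offset, so that the T1 window of about 61 days is comparable with the 90-day windows at T0, T2 and T3.

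The cost is a sentence or two. Use is recorded by day, so the cut is made in data already collected, with no extra visit or participant burden. Fixing the rule before analysis also rules out a later choice of window. The small downside is a shorter T1 window, and so a somewhat less precise estimate of each participant's use at that visit.
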